### 2.6. Statistical Analysis

The distribution of quantitative variables will be analyzed with the Kolmogorov– Smirnov test, to evaluate the normality of the samples to verify if there are significant differences in the two samples at baseline, as well as at different times (*p* > 0.05). The t-test will be used for comparison of characteristics between the different groups at baseline. The chi-square test will be used to assess the independence of the categorical baseline data. The mean, SD and 95% CI will be calculated for all variables. Repeated-measures analyses of variance (ANOVA) with two factors (2 (treatment groups) × 5 (time: baseline, immediately after intervention, and at one month, two months and three months after the study started)) will be performed for the FIQ and NPRS scores. The comparisons for time factor for all variables and for each group will be applied to the group. Time comparisons for all variables and for each group the proportion of subjects who have an improvement than the NPRS MCID (2.0 points) or the FIQ MCID (14%) will be calculated and will be compared between groups using the *p* value [26,49]. The effect size will be calculated for the NPRS and FIQ variables. *p* values associated with F statistics will be adjusted for ANOVA via the Greenhouse–Geisser correction. Statistical significance will be set at *p* value of <0.05 for all calculations. 

For the analysis of the pilot study, the data were analyzed with the SPSS package version 25.0 (SPSS Inc, Chicago, IL, USA). The homogeneity of the sample in both groups was examined at the beginning of the study with respect to the variables studied to detect statistically significant differences using the Mann–Whitney U test. Descriptive statistics, including frequency counts for categorical variables and measures of central tendency and dispersion for continuous variables, were calculated to summarize the data. Paired-samples T-test was used to compare pre, post, and 1–2-month measurements of all variables studied. The Wilcoxon rank test for related samples was used to establish differences between scores before and immediately after the 4 treatment sessions, 1 month after the intervention and 2 months after the intervention in the two groups. For all study data, *p* values less than 0.05 were considered significant.

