#### Sample Size

The latest version of the free GRANMO program version 7.12 was used. The sample size of 52 randomly distributed patients will provide at least 80% statistical power to detect a difference of 14 units between the two groups in the FIQ inventory. This calculation assumes a bilateral significance level of 5% and a standard deviation of 17. In addition, a loss rate of 10% was calculated until the end of the study.

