### 2.4. Randomization and Blinding

To ensure adequate blinding, participants will be randomly assigned to either the MMA (Maitland’s mobilization approach) group or the MTA (myofascial techniques approach) group immediately after they sign the informed consent forms. The randomization process will use numbers in sequential opaque envelopes. Patients will be asked not to comment on the treatment to other participants or to the evaluators. Details of adverse events will be recorded in a document which will be given to an administrator and completed separately by subjects in a room before the next session. Graph Pad software will be used to perform randomization, which will include the MMA group and the MTA group [27]. 

Thirteen patients were also evaluated, treated and reevaluated for the pilot study. Using a non-probability method of judgmental or purposive sampling, eight patients were assigned to the MTA group and five to the MMA group.

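### The 2 x 5 repeated-measures ANOVA counts baseline as an outcome level and names no F term or visit as the treatment test, so it does not test the 14-unit FIQ difference the trial was sized for

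*Protocol article*

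**What the plan says.** Sample Size section: the trial is to have "at least 80% statistical power to detect a difference of 14 units between the two groups in the FIQ inventory". The inputs are given in one sentence: "This calculation assumes a bilateral significance level of 5% and a standard deviation of 17". The total is 52, and "a loss rate of 10% was calculated until the end of the study". No time point is attached to the 14 units.

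Section 2.6: the comparison of the arms over time is "Repeated-measures analyses of variance (ANOVA) with two factors", applied to FIQ and NPRS only. The factors are group (2) and time (5): baseline, straight after treatment, and one, two and three months from study start. The F-test p values get a Greenhouse-Geisser correction. The section does not say whether the group term, the time term or their interaction is the treatment test, and names no visit for a contrast between the arms.

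Baseline enters one other way: "The t-test will be used for comparison of characteristics between the different groups at baseline". It is not used as a covariate. Neither section gives a rule for missing visits.

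**The concern.** The trial asks which of two manual therapies works better. The sizing turns that into one number, a 14-unit FIQ difference between arms. The planned ANOVA offers two terms that involve group, and neither is that number.

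- **Group main effect.** It compares the arms on the average of five visits, one of which precedes treatment. Randomisation makes the expected baseline difference zero, so the quantity tested is smaller than the treatment effect.
- **Group x time interaction.** It has 4 degrees of freedom and detects any departure from parallel profiles. A significant result gives no visit, direction or size.

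With no term named, either could be reported as the treatment test once results are known, and the stated power belongs to neither. There is also a likely problem with incomplete patients: the classical form of this ANOVA ordinarily needs all five values, and the plan expects losses.

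**Working it through.** **1. The plan's own figure.** Inputs from the Sample Size section: difference 14, SD 17, two-sided 5%, 80% power, 10% loss. Equal allocation is assumed because no ratio is stated.

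n per arm = 2 x (17 x (1.960 + 0.842) / 14)^2 = 23.15. Allowing for loss, 23.15 / 0.9 = 25.72, so 26 per arm, or 52. The stated total reproduces as a plain comparison of two means at one time. After 10% loss, 26 x 0.9 = 23.4, taken as 23 per arm. A two-sample t-test then has 78% power (83% at 26 per arm).

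**2. What each term tests.** With a sustained effect the group differences over the five levels are 0, 14, 14, 14, 14. Their mean is 56/5 = 11.2, which is the main-effect difference.

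**3. Power formulas.** Assumed: n = 23 per arm, SD^2 = 289, compound symmetry, correlation r = 0.3, 0.5 or 0.7. The article gives no correlation. Noncentral F, two-sided 5%. Below, d is the group difference at a visit and dbar its mean over the five levels.

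- Interaction, 4 and 176 df: noncentrality = (n/2) x sum(d - dbar)^2 / [289(1 - r)]
- Main effect, 1 and 44 df: noncentrality = (n/2) x dbar^2 / [289(1 + 4r)/5]
- One baseline-adjusted visit, 1 and 43 df: residual variance 289(1 - r^2)
- Baseline-adjusted mean of four post-baseline visits, 1 and 43 df: residual variance 289[(1 + 3r)/4 - r^2]

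**4. Sustained effect, worked at r = 0.5.**

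- Interaction: sum of squares = 11.2^2 + 4 x 2.8^2 = 156.8; noncentrality 11.5 x 156.8 / 144.5 = 12.48; power 81%.
- Main effect: 11.5 x 125.44 / 173.4 = 8.32; power 81%.
- One adjusted visit: 11.5 x 196 / 216.75 = 10.40; power 88%.
- Adjusted mean of four: 11.5 x 196 / 108.375 = 20.80; power 99%.

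Simulation with the Greenhouse-Geisser correction (4,000 runs, r = 0.5) gave 80% for the interaction, 81% for the main effect and 88% for one adjusted visit.

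**5. Fading effect (14, 9, 4, 0).** The pilot suggests this shape. From Tables 2 and 3, MMA minus MTA mean FIQ is 58.41 - 44.07 = 14.34 after treatment, 51.66 - 41.33 = 10.33 at one month and 49.07 - 44.78 = 4.29 at two months. The pilot had 13 non-randomised patients with a baseline gap of 54.87 - 52.28 = 2.59, and the final 0 is assumed. Here dbar = 27/5 = 5.4, sum(d - dbar)^2 = 147.2, and the mean of the four post-baseline differences is 6.75.

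**6. Results, power at r = 0.3 / 0.5 / 0.7.**

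| Test | Sustained 14 | Fading 14, 9, 4, 0 |
|---|---|---|
| ANOVA interaction | 65 / 81 / 97% | 61 / 78 / 96% |
| ANOVA group main effect | 91 / 81 / 71% | 36 / 28 / 23% |
| Adjusted, first post-treatment visit | 82 / 88 / 97% | 82 / 88 / 97% |
| Adjusted, mean of four post-baseline visits | over 99% at each | 56 / 58 / 69% |

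Under fading, the adjusted comparison at the second, third and fourth post-baseline visits has 45/53/69%, 13/15/19% and 5%.

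**7. Missing visits.** If the planned 10% is plain dropout, complete-case analysis loses about 10%, which the 52 already allows for. If instead 5% miss each of four post-baseline visits independently, the loss is 1 - 0.95^4 = 18.5%, leaving about 42 of 52. The 5% is an assumption. In the pilot, 1 of 13 missed a visit.

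**The case against.** A 2 x 5 ANOVA with baseline as a level is a valid analysis of a randomised trial. Its interaction tests whether the arms change differently, so baseline is not ignored. At correlation 0.5 with a sustained effect, both ANOVA terms have more power than the unadjusted 78%. That all stands: this is a mismatch and an efficiency point, not an invalid test.

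Four stronger readings are tempting, and the article does not support them.

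- **The plan drops patients with a missing visit.** It does not say so. Listwise deletion is how the classical method ordinarily works, and a missing-data rule may sit in a fuller document.
- **The ANOVA always wastes power that a mixed model gives for nothing.** At correlation 0.7 with a sustained effect the interaction equals a single adjusted visit (97%), and at 0.3 the main effect beats it (91% against 82%). Under fading, the interaction beats the adjusted mean of the four visits at every correlation. The alternative model brings choices and assumptions of its own.
- **The planned analysis has only 23 to 36% power.** That is the main effect under a fading profile; the interaction has 61 to 96% there.
- **No estimate with an interval is planned.** Means with 95% CIs, an effect size for NPRS and FIQ, and a comparison of responder proportions are planned. What is absent is a named difference between arms with its CI.

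Separately, section 2.5 calls WPI and symptom severity the two primary outcomes, while the sizing uses FIQ and the ANOVA covers FIQ and NPRS. That needs reconciling in its own right and does not remove this point.

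**Conclusion.** The point holds as a mismatch between sizing and analysis. The 52 is right for a single two-group FIQ difference of 14, and neither group term of the planned ANOVA is that difference: one tests a diluted 11.2 for a sustained effect, the other an unspecified departure over 4 degrees of freedom. This rests on the article's text alone.

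The cost in power is conditional. It rests on SD 17, compound symmetry, 23 per arm and an assumed correlation, and it changes with the effect profile, the term read and the contrast put in its place. For a sustained effect, the baseline-adjusted mean of the four visits clearly beats both terms. For a fading effect, the adjusted first post-treatment visit does at least as well as either, and later visits do much worse. Loss of incomplete patients is a likely further cost but an inference. The change should be made before outcome data are examined by arm.

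**What to change.** Replace the ANOVA in section 2.6 with a linear mixed model on all available post-baseline values, with group, visit, group x visit and the baseline score as covariate. Name one primary contrast in advance, for example the FIQ difference between arms at one stated visit. Report it with its 95% CI, and state in the Sample Size section that the 14 units refer to it.

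When choosing the visit, define the schedule clearly. With four weekly sessions, the assessment straight after treatment and the one a month from study start fall at about the same time.

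Cost: a change of analysis wording and no new data. The downside is that the visit, the covariance structure and a missing-at-random assumption must be chosen and defended. An unfortunate choice of visit gives up much of the gain if the effect fades.

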## 2. Materials and Methods

### 2.1. Study Design

A randomized controlled clinical trial (RCCT) with a 3-month follow-up will be carried out between January 2023 and July 2023, with 52 female patients affected by rheumatologist-diagnosed FM who will be recruited and evaluated at the Asociación de Fibromialgia y Síndrome de Fatiga Crónica (AFINSYFACRO) in Móstoles, Madrid, Spain. The study protocol was approved by the Ethical Committee of the Rey Juan Carlos University, Madrid, Spain (reference number 2609202220822). In addition, the study was registered with ClinicalTrials.gov (NCT05559021), and will be conducted in accordance with CONSORT Statement 2010: updated guidelines for reporting parallel group randomized trials (CONSORT 2010 flowchart, Figure 1). According to the Declaration of Helsinki, all patients will sign an informed consent form before inclusion and must agree that their clinical information will be published anonymously. 

For more details on the protocol, a pilot study was carried out between January 2022 and July 2022 by recruiting thirteen patients using a non-probability method of judgmental or purposive sampling. The study protocol was approved by the Ethical Committee of the Rey Juan Carlos University, Madrid, Spain (reference number 2609202220822). All patients signed an informed consent form before inclusion.

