#### 2.3.1. MMA Group

After a literature review of manual therapy treatments for fibromyalgia patients [16,24,25] and through a consensus of experts with 15–20 years of clinical experience, there was a decision to perform the following passive mobilizations approach for 1 session per week of 30 min each, for a total of 4 weeks.

The MMA group will be carried out with patient lying in a prone position, with the hands around the body and neck positioned comfortably. The therapist will perform postero-anterior joint mobilization using Maitland’s technique, applying pressure on the spinous process of the target vertebra (the one which most reproduces patient’s symptoms) [24]. Amplitude of mobilization will be done according to patient’s irritability, as other studies recommended [25]. Cycles of joint mobilizations will be applied to lumbar spine (Figure 2), thoracic spine (Figure 3) and cervical spine (Figure 4). 

In addition, it was decided to perform 3 sets of 2 min duration with 1 min of rest in each painful segment of the cervical, thoracic and lumbar spine. Spinal mobilizations have greater global, systemic and pain-modulating reflexogenic effects than peripheral joint mobilizations, so it was decided in expert consensus to select this approach targeting the spine with joint mobilizations [16,23,24,25].

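### Section 2.6 counts the trial's follow-ups from study start although treatment takes 4 weeks, so as written the one-month visit nearly repeats the post-treatment visit and the last visit is about 2 months after treatment

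*Protocol article*

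**What the plan says.** The protocol article gives timing information in four places.

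- **Treatment length.** Section 2.3.1 gives the MMA arm "1 session per week of 30 min each, for a total of 4 weeks". Section 2.3.2 gives the MTA arm the same frequency and duration.
- **Trial assessments.** Section 2.6 plans a 2 × 5 repeated-measures ANOVA for FIQ and NPRS. The time factor begins "time: baseline, immediately after intervention, and at one month" and the follow-up levels are dated "at one month, two months and three months after the study started".
- **Pilot assessments.** The second paragraph of 2.6 dates the pilot visits "1 month after the intervention and 2 months after the intervention in the two groups". Sections 3 and 4 use the same clock. Section 3 presents the pilot as a preliminary application of the protocol, and section 4 says that it is meant to show how the trial will develop.
- **Label.** Section 2.1 describes "A randomized controlled clinical trial (RCCT) with a 3-month follow-up will be carried out between January 2023 and July 2023". Neither it nor the abstract says from which event the 3 months run.

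**The concern.** The trial paragraph of 2.6 uses study start as its clock and the pilot paragraph uses the end of treatment, for visits with the same names. The 4-week course lies between the two clocks, so they differ by nearly a month.

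If the start clock is applied as written, one of the four post-baseline assessments comes only days after another and says little about whether an effect lasts. The longest post-treatment interval is then nearer 2 months than 3. A one-month result from the trial would also not mean the same as a one-month result from the pilot. Section 4 itself describes a pain effect that weakens after treatment and asks for longer follow-up, so persistence is one of the questions the trial should answer.

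**Working it through.** **Inputs.** Four weekly sessions over 4 weeks (2.3.1, 2.3.2); follow-ups at 1, 2 and 3 months from start (2.6); pilot means (Tables 2 and 3).

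**Assumptions.** The article gives no visit days. I take study start as each patient's own start, with the first session on day 0 and sessions on days 0, 7, 14 and 21. The end of treatment is then day 21 (fourth session) or day 28 (end of week 4). One month is 30.44 days.

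**Formulas.** Under the start clock, interval after treatment = k × 30.44 − E, with k = 1, 2, 3 months and E = 21 or 28. Under the end-of-treatment clock, day from start = E + k × 30.44.

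| Visit | Day from start, as written | Days after treatment (E = 28 / E = 21) | Months after treatment | Day from start if counted from end of treatment (E = 21 / E = 28) |
|---|---|---|---|---|
| 1 month | 30.4 | 2.4 / 9.4 | 0.08 / 0.31 | 51.4 / 58.4 |
| 2 months | 60.9 | 32.9 / 39.9 | 1.08 / 1.31 | 81.9 / 88.9 |
| 3 months | 91.3 | 63.3 / 70.3 | 2.08 / 2.31 | 112.3 / 119.3 |

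The two clocks differ by 21 to 28 days at every follow-up visit.

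**Overlap of recall windows.** The WPI asks about the last week (2.5.1). If the post-treatment visit is on day 28, the WPI windows at that visit and at one month share 7 − 2.4 = 4.6 days. If it is on day 21, they do not overlap (9.4 > 7). The PSQI covers the prior month (2.5.5), so at day 30 it describes mostly the treatment period under either assumption.

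**Does the anchor change what one month would show?** Pilot NPRS means in the MTA group were 6.13 at baseline, 3.13 immediately after treatment and 5.63 one month after treatment.

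- Improvement at end of treatment: 6.13 − 3.13 = 3.00 points.
- Improvement one month after treatment: 6.13 − 5.63 = 0.50 points.
- Difference between the two times: 5.63 − 3.13 = 2.50 points.

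The NPRS threshold used in 2.6 to count improvers is 2.0 points. The mean change is above it at one time and below it at the other. This group had 8 patients and was not randomised, so the figures show that timing can matter, not how much it will.

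**Sample size.** The plan states "at least 80% statistical power to detect a difference of 14 units between the two groups in the FIQ inventory" with a "bilateral significance level of 5% and a standard deviation of 17". By the normal approximation, n per arm = 2 × (17 × (1.960 + 0.842) / 14)² = 23.15. Allowing for 10% loss, 23.15 / 0.9 = 25.7, so 26 per arm and 52 in total. The plan's figure reproduces, and visit timing does not enter it.

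**The case against.** The strongest reply is that the phrase is loose drafting. The end-of-treatment assessment and the one-month assessment are separate levels, which makes little sense if they are days apart, and the pilot used the end of treatment. On that reading no visit moves and only the wording needs correcting. This is plausible and cannot be excluded. But the trial paragraph of 2.6 is the only place that dates the trial's follow-ups, and it says study start. Visit timing in the flow diagram, if any, cannot be checked because the figure is not shown.

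Counting from the start is also a legitimate choice, and an unanchored 3-month follow-up is compatible with it. That stands. It makes the label incomplete rather than false.

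The visit days are assumed. At the upper end, a visit 9 days after the last session is close to the post-treatment visit but not a duplicate of it.

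Three stronger readings are tempting, and the documents do not support them.

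- *The treatment comparison is biased.* Both arms have the same 4-week course, so the clock shifts both equally.
- *The trial is underpowered because of this.* The 14-unit FIQ difference is not tied to any visit, and 52 reproduces.
- *The pilot effect faded between 1 and 2 months after treatment.* NPRS in the MTA group was already back to 5.63 at one month (p = 0.518). Its FIQ means were 44.07, 41.33 and 44.78 at post-treatment, one and two months, against 52.28 at baseline. The FIQ p-value changed (0.036 to 0.31), but the two-month mean is close to the post-treatment mean.

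**Conclusion.** The point holds as an unreconciled follow-up anchor with a definite consequence if the text is followed. As written, the one-month visit is about 2 to 9 days after treatment ends and the final visit about 9 to 10 weeks after it, against 3 months (about 13 weeks) under the pilot's clock. Two of the five ANOVA levels are nearly redundant, and persistence of effect is less well measured than the schedule suggests. This rests on study start meaning each patient's own start and on sessions keeping to the weekly schedule. A single calendar start date would not work for consecutively recruited patients.

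It is a moderate point. It does not threaten the validity of the randomised comparison, but it should be settled before the first follow-up is booked, because an assessment taken at the wrong time cannot be recovered.

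**What to change.** State one anchor for the 1-, 2- and 3-month assessments and use it in the abstract, 2.1 and 2.6. Counting from the last treatment session is preferable: it matches the pilot, separates the five time levels and makes the 3-month label true of the post-treatment period.

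If the wording was loose, the cost is one phrase. If the start clock was intended, each patient's last assessment moves about 3 to 4 weeks later, from about day 91 to about day 112–119. That needs checking against the January to July 2023 window. Taking both months in full gives 212 days, so the time available for patients to start falls from about 212 − 91 = 121 days to about 212 − 119 = 93 up to 212 − 112 = 100 days. A modest extension may be needed.

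If the start anchor is kept, say so in 2.1 and the abstract, describe the final assessment as about 2 months after treatment, and note that the one-month visit is not comparable with the pilot's. The sample size needs no change either way.

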### 2.3. Intervention

There will be two intervention groups: myofascial techniques approach (MTA) group and Maitland’s mobilization approach (MMA) group. Both interventions were conceived and were (pilot study) and will be (RCCT) developed by clinicians and professors of Manual Therapy at the European University of Madrid (Spain), the Complutense University of Madrid (Spain), and CEU-San Pablo University of Madrid (Spain), with more than 15–20 years of clinical experience ([name]; [name]; [name]; [name]; [name]; and [name]). The research team includes two doctors in physiotherapy and four doctoral students, as well as a doctor in psychology. Only [name] had 2 years of clinical experience and a Master of Science degree.

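### An unadjusted p < 0.05 applies to all calculations and no test is marked as confirmatory, so the chance of a false claim that one approach is more effective is not controlled

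*Protocol article*

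**What the plan says.** Section 2.6 (Statistical Analysis) sets the rule for the planned trial: "Statistical significance will be set at *p* value of <0.05 for all calculations". The tests it plans on outcomes are:

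- 2 × 5 repeated-measures ANOVAs (group by time) for FIQ and NPRS;
- a between-group comparison of the proportions reaching the NPRS and FIQ MCIDs, judged by a p value;
- time comparisons for every variable: "The comparisons for time factor for all variables and for each group will be applied to the group".

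The only p-value adjustment named is Greenhouse–Geisser, which corrects for non-sphericity and not for the number of tests.

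The Sample Size section rests on one FIQ comparison of the arms: 52 patients are to give at least 80% power for a 14-unit difference. Its error level and spread are stated as follows: "This calculation assumes a bilateral significance level of 5% and a standard deviation of 17". Section 2.5 names the two ACR 2010 tools, WPI and SS-Score, as the primary outcomes. The introduction states the aim as finding which approach is more effective across sensory, cognitive, emotional and social symptoms.

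**The concern.** The trial asks one comparative question of many outcomes at several visits. Three sections point to three different places for the confirmatory test: WPI and SS (section 2.5), FIQ (Sample Size), and FIQ with NPRS (section 2.6). Under a flat 0.05 rule, any of the planned results could be used to declare one approach superior, and nothing in the text says which may not. A reader of the final report could not tell a pre-specified positive result from the most favourable of several chances. This is a rule the article states; it is not a detail merely left out.

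**Working it through.** **1. The plan's own figure.** Inputs from the Sample Size section: difference 14, SD 17, two-sided 5%, power 80%, loss 10%. Equal allocation to the two arms is assumed.

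n per arm = 2 × [17 × (1.960 + 0.842) / 14]² = 23.15; 23.15 / 0.9 = 25.7, rounded up to 26; N = 52. The stated figure reproduces. It refers to one FIQ contrast, whose own error rate is 5%.

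**2. What the rule covers.**
- Between groups: FIQ and NPRS only. Two group-by-time F tests; two group main-effect F tests if these are read as well; two responder comparisons at a number of visits that the article does not state.
- Within arms: 13 outcomes can be compared with baseline (WPI, SS, FIQ, EQ-5D-5L, NPRS, CSI, PSQI, IPAQ, TSK, STAI, BDI-II, GHQ-12, PSEQ; GRoC is itself a change rating and is left out). One overall time test per outcome and arm gives 13 × 2 = 26 tests. Each of four follow-ups against baseline gives 13 × 4 × 2 = 104. The sentence on time comparisons is unclear and fits either reading.

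**3. Independent-test benchmark.** P(at least one p < 0.05) = 1 − 0.95^m.

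| m | Result |
|---|---|
| 2 | 9.75% |
| 4 | 18.5% |
| 26 | 73.6% |
| 104 | 99.5% |

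The tests are correlated, so simulation is needed.

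**4. Between-group tests on FIQ and NPRS, no treatment difference.** Assumptions that the article does not give: normal scores; correlation 0.3–0.5 between the two outcomes and 0.5–0.7 between visits; 23 completers per arm (26 × 0.9 = 23.4). For responders: FIQ mean 53, SD 17; NPRS mean 6.3, SD 1.5; chi-square tests. The ranges span these settings and repeated runs.

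| Tests counted | At least one p < 0.05 |
|---|---|
| Two group-by-time F tests | about 7–10% |
| Plus two group main effects | 14–20% |
| Group-by-time plus responders at one visit | 14–17% |
| Group-by-time, main effects, and responders at all four follow-ups | about 33–43% |

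**5. Within-arm tests, no change over time in either arm.**
- 26 overall time tests: 73% at outcome correlation 0, 59% at 0.5, 45% at 0.7, 28% at 0.9.
- 104 tests against baseline (visit correlation 0.5): 98% at outcome correlation 0.2, 93% at 0.5, 85% at 0.7, 66% at 0.9.

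The span is about 28–98%, depending on the reading and the correlations.

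**6. Power if alpha is shared by two confirmatory tests** (t test, d = 14/17; the worst case under Holm is 0.025 for the FIQ test):

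| Per arm | alpha 0.05 | alpha 0.025 |
|---|---|---|
| 26 | 0.83 | 0.74 |
| 23 | 0.78 | 0.68 |

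The 0.78 against the stated 80% reflects the t distribution and rounding down to 23. The normal formula at 23.4 per arm gives 0.80, so this is not a separate fault.

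**The case against.** The strongest case against is that the article condenses a fuller protocol, that multiplicity is commonly settled in an analysis plan, and that the planned between-group tests are few. The ANOVAs, effect sizes and responder comparisons are confined to FIQ and NPRS, and section 2.6 nowhere says that a within-arm p value supports superiority. Much of this stands. The between-group inflation is moderate unless responders are tested at every visit, and neither the visits nor the responder test is stated. What does not stand is that the matter is simply left open: the article fixes 0.05 for all calculations, and an analysis plan with any hierarchy would have to override that sentence.

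Three stronger readings are tempting and are not supported.

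- A reader might infer that the 5% in the sample size is wrong. It is the level of one FIQ comparison and carries no promise about the whole set of tests; it remains true.
- A reader might take the high within-arm percentages as a property of the plan. They depend on an unclear sentence, on correlations not given, and on a null of no change over time in either arm. That null is stronger than no difference between treatments.
- A reader might note that none of the pilot's 60 tests (10 outcomes × 3 times × 2 arms, Table 3) passes a Bonferroni limit of 0.05/60 = 0.0008. That shows nothing. The smallest exact two-sided Wilcoxon p is 2/2⁸ = 0.0078 with 8 patients and 2/2⁵ = 0.0625 with 5, so untied data could not have reached the limit.

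**Conclusion.** The point holds in a limited form. Section 2.6 states a rule that leaves the overall chance of a false superiority claim uncontrolled, and no section identifies the test that carries the 5%. For the comparison the trial is about, the inflation on FIQ and NPRS runs from about 7–10% to about 33–43%, according to how many of the named tests are read as evidence. These figures assume the correlations above, 23 per arm and, at the upper end, responder tests at all four follow-ups. Within-arm testing of all 13 outcomes adds many more chance findings, but these mislead about relative effectiveness only if they are read as a comparison of the arms. The conflict between the primary outcomes and the sample size aggravates the problem, because it leaves no default confirmatory test.

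**What to change.** First reconcile the primary outcomes in section 2.5 with the sample size and section 2.6. Then replace the significance sentence in section 2.6 with wording such as:

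> The two-sided 5% level applies only to the pre-specified confirmatory between-group test(s) on [outcome(s), time point]. If there are two, Holm's procedure is applied across them. Responder proportions, other visits, other outcomes and within-group changes are reported as estimates with 95% confidence intervals, are labelled exploratory, and cannot on their own support a conclusion that one approach is more effective.

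**Cost.** With one confirmatory test this is a change of wording with no loss of power. With two, worst-case power for the 14-unit FIQ difference falls from 0.83 to 0.74 at 26 per arm, and from 0.78 to 0.68 at about 23 per arm after 10% loss. If WPI and SS are kept as the confirmatory pair, the cost cannot be worked out from the article, which gives no target difference for either; a new sample size statement would be needed.
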